## Efficacy analyses

All non-inferiority hypotheses will be tested on a one-sided level of significance α=0.025. All superiority hypotheses will be tested on a two-sided level of significance α=0.05.

### Definition and analysis of primary endpoint

Change in IOP between baseline and three months post-OP was defined as the primary efficacy variable. A non-inferiority test will be carried out with to show that treatment with Cosopt-S® is not inferior to the standard preoperative treatment. An ANCOVA model will be implied including the IOP baseline value as a covariate. Δ = 4 mm Hg is specified as the non-inferiority limit. The significance level  is fixed at 0.025 to account for the one-sided testing situation. The primary analysis will be done for the per protocol population. The analysis will be repeated for the ITT population. Additionally, the 95% confidence interval for treatment differences will be displayed to check and to visualize the non-inferiority test results.

### Analysis of secondary endpoints

Two-sided significance tests with  = 0.05 will be carried out for the following secondary and tertiary efficacy variables on an exploratory basis: Change in IOP between Visit 1 and Visit 2 will be investigated by means of an ANCOVA model including the baseline value as a covariate. The number of necessary 5FU injections and sture lyses, needlings and reoperations as well as the change in vision development will be tested between groups by means of the Wilcoxon-Mann-Whitney test. The ocular hypotension rate will be compared by a Chi-Square test. The NEI VFQ 25 quality of life questionnaire (composite score and subscales) will be analysed by a linear model with repeated measurements. The same method is employed for the patients’ satisfaction. The ORA redness scale will be compared by the Wilcoxon-Mann-Whitney test. For the change in the filtering bleb classification descriptive statistics will be presented only.

All other target criteria and demographic, anamnestic and safety data will be analysed by descriptive statistical methods, i.e. quantitative data will be described by valid N, mean, standard deviation, minimum, median and maximum, qualitative and ordinal variables will be presented by means of distribution functions. Appropriate inferential statistical methods will be employed. All analyses of secondary endpoints will be interpreted purely exploratory.

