## Secondary endpoints

- Safety and tolerability of both treatment arms: Analysis of adverse events and questionnaires.
- Number of necessary 5FU injections and suture lyses at Visit 5
- Required number of needlings and reoperations at Visit 5
- Change in IOP between Visit 1 and Visit 2
- Comparison between both groups of ocular hypotension rate (IOP 0-5 mm Hg, shallow anterior chamber, Descemet’s folds, choroid swelling, macular and choroidal folds) and filtration bleb classification in both groups at every postoperative visit.
- Change in quality of life for the two regimens based on the NEI VFQ 25 quality-of-life questionnaire between Visit 1, Visit 2 and Visit 5 in both groups
- Patients’ satisfaction with pharmacologic intervention for IOP lowering between Visit 1, Visit 2 and Visit 5 in both groups based on a visual analogue scale
- Change in the conjunctiva status between Visit 1 and Visit 2 in both groups

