# TRIAL schedule

Visit 1 (Screening visit): -16 to -4 weeks

The following data will be obtained/checked and documented:

- Patient information and informed consent
- Age
- Gender
- Medical history and concomitant medications
- In- and exclusion criteria
- Best corrected distance visual acuity (ETDRS charts)
- IOP (GAT) (schedule to return for all visits at the same time (± 1 hour) as Visit 1.
- Slitlamp examination (biomicroscopy)
- Grading of conjunctiva (ORA redness scale)
- Photography (conjunctiva)
- Non-contact pachymetry
- Symptom survey / Questionnaires
- Urine pregnancy test if the patient is a woman of childbearing potential
- Patient instruction: patients have to discontinue their current glaucoma medication(s), starting 28 days prior to surgery
- Randomisation
- Dispense of medication, explanation of application
- Dispense of follow-up booklet
- Schedule the patient to return for the next visit, according to date of planned surgery

Visit 2: Day -1

- Changes in medical health and/or concomitant medication
- Adverse events
- Last day of administration of study drugs
- Collection of study medication after last dose
- Checking compliance
- Symptom survey / Questionnaires
- Best corrected distance visual acuity (ETDRS charts)
- IOP (GAT) at the same time as Visit 1 (± 1h)
- Non-contact pachymetry
- Optical coherence tomography
- Axial length (IOL Master)
- Anterior chamber depth (AC or IOL Master)
- Slitlamp examination (biomicroscopy)
- Grading of conjunctiva (ORA redness scale)
- Photography (conjunctiva)
- Schedule the patient to return for the next visit

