**14.4 ORA Redness Scale**

Redness of the conjunctiva will be graded by *ORA Redness Scale* (Grade 0-4).

0 = none (normal)

1 = mild (a flush reddish colour predominantly confined to the palbebral or bulbar conjunctiva)

2 = moderate (more prominent red colour of the palbebral or bulbar conjunctiva)

3 = severe (definite redness of palbebral or bulbar conjunctiva)

4 = very severe (severe redness of palbebral and bulbar conjunctiva)

[figure not shown]

Supplement: S1 File — (DOC) [file pone.0171636.s001.doc]

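### Section 7.3.2 compares conjunctival redness by a Wilcoxon test with no Visit 1 covariate and does not say what is ranked; a baseline-adjusted rank analysis is a free, minor improvement

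*Protocol*

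**What the plan says.** Protocol section 7.3.2 (Analysis of secondary endpoints) fixes the redness test in one sentence: "The ORA redness scale will be compared by the Wilcoxon-Mann-Whitney test". Vision is handled in the same paragraph: the counts of 5-FU injections, suture lyses, needlings and reoperations "as well as the change in vision development will be tested between groups by means of the Wilcoxon-Mann-Whitney test". Neither test has a covariate.

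Section 3.4 defines the redness endpoint as "Change in the conjunctiva status between Visit 1 and Visit 2 in both groups". The visit list in section 5 has the ORA grade at Visits 1 and 2, and best-corrected acuity at Visit 1 and at every later visit. Appendix 14.4 shows that the redness scale is ordinal, with grades 0 to 4.

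IOP is treated differently. For the secondary endpoint, "Change in IOP between Visit 1 and Visit 2 will be investigated by means of an ANCOVA model including the baseline value as a covariate". For the primary endpoint (section 7.3.1), "An ANCOVA model will be implied including the IOP baseline value as a covariate".

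Section 7.3.2 also says that all secondary analyses are to be interpreted as purely exploratory. Section 7 lets the SAP modify the plan and requires a protocol amendment only for major changes to the primary endpoint or its analysis.

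**The concern.** The Visit 1 redness grade is collected, but the named test does not use it as a covariate, and the sentence leaves open what is compared. Each reading has a cost:

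- **Change is ranked.** The Visit 1 noise is added to the Visit 2 noise. A step from 0 to 1 counts the same as a step from 3 to 4, and an eye that starts at 0 can only stay or worsen.
- **Visit 2 grade is ranked.** The Visit 1 grade is discarded.

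The trial's rationale (sections 1.1 and 4.1.1) is that a preservative-irritated conjunctiva promotes scarring of the bleb. Redness between Visits 1 and 2 is the formally tested measure of whether preoperative treatment calms the conjunctiva, since the change in bleb classification is only described. What is at stake is the sensitivity of that exploratory comparison in a trial of 60 patients.

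**Working it through.** **The plan's own figure.** Section 7.1 gives 26 evaluable patients per arm for the primary IOP test (margin 4 mm Hg, SD 5 mm Hg, one-sided alpha 0.025, beta 0.20). The normal formula gives 2 × (1.96 + 0.842)² × 5² / 4² = 24.5, so 25 per arm. The exact noncentral t gives power of about 79% at 25 and 81% at 26, so 26 is reproduced. With 60 enrolled, 1 − 52/60 = 13.3% may be non-evaluable, in line with the stated allowance of a bit more than 10%. Nothing below changes these figures. The protocol plans no power for redness or vision.

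**Theory.** Let rho be the correlation between Visit 1 and Visit 2. Relative to a test on Visit 2 alone, the residual variance is:
- Visit 2 alone: 1
- change score: 2(1 − rho)
- baseline-adjusted: 1 − rho²

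The adjusted variance never exceeds either of the others. The ratio of change score to adjusted is 2(1 − rho)/(1 − rho²) = 2/(1 + rho), which is 1.67 at rho 0.2 and 1.11 at 0.8. The change score beats Visit 2 alone only when 2(1 − rho) < 1, that is, when rho > 0.5.

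For a two-sided alpha of 0.05 and an effect that gives Visit 2 alone 80% power, power = Φ(2.802/√v − 1.96), where v is the relative variance. At rho 0.3, v = 1.4 for the change gives 66% and v = 0.91 for the adjusted analysis gives 84%. At rho 0.7, v = 0.6 gives 95% and v = 0.51 gives 98%.

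**Simulation on a five-grade scale.** Assumed, because the documents give neither: a latent shift of 0.7 SD and the value of rho. The latent variable was cut at −1.0, 0, 0.9 and 1.8, with 20,000 runs per setting, a tie-corrected Wilcoxon test and Quade's rank ANCOVA. Power in %:

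| Per arm | rho | Wilcoxon, Visit 2 | Wilcoxon, change | Rank ANCOVA | Loss, Visit 2 | Loss, change |
| --- | --- | --- | --- | --- | --- | --- |
| 26 | 0 | 63.3 | 34.5 | 63.0 | −0.3 | 28.5 |
| 26 | 0.3 | 63.6 | 44.7 | 66.0 | 2.4 | 21.3 |
| 26 | 0.5 | 63.5 | 55.6 | 72.5 | 9.0 | 16.9 |
| 26 | 0.7 | 63.2 | 72.5 | 82.8 | 19.6 | 10.3 |
| 30 | 0 | 70.3 | 39.2 | 69.7 | −0.6 | 30.5 |
| 30 | 0.3 | 70.0 | 49.8 | 72.3 | 2.3 | 22.5 |
| 30 | 0.5 | 69.2 | 61.5 | 77.7 | 8.5 | 16.2 |
| 30 | 0.7 | 69.2 | 79.3 | 88.2 | 19.0 | 8.9 |

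Type I error was 4.7 to 5.2% for all three methods. A separate simulation with 28 per arm and the same shift gave, for Visit 2 / change / rank ANCOVA:
- rho 0.2: 68/46/69%
- rho 0.4: 67/57/73%
- rho 0.6: 67/71/82%
- rho 0.8: 68/91/94%, so losses of 94 − 68 = 26 points for Visit 2 and 94 − 91 = 3 points for the change

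Type I error there was about 4 to 6% for all three. At rho 0 the plain Visit 2 test is ahead of rank ANCOVA by less than 1 point, so the two are effectively equal there.

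**Vision.** This was not simulated. Only the variance ratio 2/(1 + rho) applies, and it approaches 1 as rho rises.

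**The case against.** A Wilcoxon test is a standard and valid choice for a five-grade ordinal scale, and ANCOVA for a continuous pressure sets no direct precedent for it. The secondary tests are declared exploratory, no power is claimed for them, and the SAP, which is not at hand, may already settle the covariate. All of this stands and limits the severity. It does not remove the point: the protocol names a method, leaves the compared quantity open, and passes over a baseline value that it collects.

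Four stronger readings might be inferred, and the documents do not support them:
- **That the planned test would declare false differences from chance baseline imbalance.** Allocation is randomised, and the simulated type I error is near 5%. An imbalance can make a particular result harder to interpret, but it does not inflate the error rate.
- **That the Visit 1 value is simply unused.** Section 3.4 defines redness as a change, and vision is explicitly tested as a change. On that reading Visit 1 is used, though inefficiently.
- **That one fixed figure describes the loss.** The size depends on a correlation and an effect that the protocol does not give, and on which quantity is ranked. The 26 per arm is also the evaluable number for IOP at three months; redness is graded before surgery, so up to 30 per arm may be available.
- **That vision suffers a loss of known size.** Vision is not listed in section 3.4, section 7.3.2 names no visit for it, and eligibility down to 20/800 makes skewed scores plausible, so a rank test is defensible there.

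**Conclusion.** The point holds as a minor, free improvement. The redness test is valid, but its sentence is ambiguous and it omits an available covariate. Under an assumed 0.7 SD shift with 26 to 30 per arm:
- If the Visit 2 grade is ranked, the loss against rank ANCOVA is about 0 to 20 points of power for correlations from 0 to 0.7, and about 26 at 0.8. It is largest at high correlation.
- If the change is ranked, the loss is about 30 points at correlation 0 and about 3 at 0.8. It is largest at low correlation.

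The direction follows from the variance formulas for any correlation; the sizes rest on the assumptions stated. For vision the same direction applies, but the gain was not quantified and is small if acuity correlates highly between visits. No primary conclusion, error rate or sample size is affected.

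**What to change.** In section 7.3.2, or in the SAP before the database is closed, state that the Visit 2 redness grade is compared between arms by rank ANCOVA (Quade): ranks of the Visit 2 grade adjusted for ranks of the Visit 1 grade, two-sided alpha 0.05. This keeps the rank-based approach, holds the type I error near 5% and settles what is compared.

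Two alternatives look less safe at this size. A Wilcoxon test stratified by Visit 1 grade (26 per arm, five equally likely grades, 0.7 SD shift, 4,000 runs) had 60% power against 64% for the plain Visit 2 test at correlation 0.2, and gained clearly only at higher correlation (73% against 63% at 0.6). A proportional-odds likelihood-ratio test rejected about 6 to 9% under the null in 400 runs per setting.

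For vision, name the visit and test the change with Visit 1 acuity as covariate, by ANCOVA or by rank ANCOVA if the scores are skewed. The choice of visit is the sponsor's.

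The cost is two sentences. No new data, visits or patients are needed, and under section 7 no protocol amendment is required, because the primary endpoint and its analysis are unchanged.

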### Interim analyses

No interim analyses are planned.

## Analysis of adverse events

All summaries and listings of safety data will be performed for the safety population.

Frequencies of subjects experiencing at least one adverse event (AE) will be displayed by body system and preferred term according to MedDRA terminology. Detailed information collected for each AE will include: A description of the event, duration, whether the AE was serious, intensity, relationship to trial drug, action taken, clinical outcome. Summary tables will present the number of subjects observed with AEs and corresponding percentages. Additional subcategories will be based on event intensity and relationship to trial drug.

A subject listing of all AEs will be prepared.

# Quality Control and Quality Assurance

## Requirements for investigational sites and staff

The investigator should be able to demonstrate (e.g. based on retrospective data) a potential for recruiting the required number of suitable subjects within the agreed recruitment period.

The investigator should have sufficient time to properly conduct and complete the trial within the agreed trial period.

The investigator should have available an adequate number of qualified staff and adequate facilities for the foreseen duration of the trial to conduct the trial properly and safely.

The investigator should ensure that all persons assisting with the trial are adequately qualified, informed about the protocol, any amendments to the protocol, the trials treatments, and their trial-related duties and functions.

## Direct access to source data/documents

The investigator/institution must permit trial-related monitoring and auditing by the IZKS Mainz, as well as inspections by the appropriate competent authorities and Ethics committees, providing direct access to source data/documents (Confidentiality see 10.3).

The subjects will be informed that representatives of the sponsor, independent ethics committee (IEC) or competent authorities may inspect their medical records to verify the information collected, and that all personal information made available for inspection will be handled in strictest confidence and in accordance with local data protection laws.

## Investigator site file and archiving

The investigator will be provided with an investigator site file (ISF) at the start of the trial. The investigator will archive all trial data and relevant correspondence in the ISF. The ISF, all source data and all documents will be kept filed according to the requirements of the ICH-GCP guidelines after termination of the trial.

After the end of the trial the investigator site file (ISF) and all other trial related documents e.g. trial master file (TMF) and CRFs will be stored in the archive of the sponsor.

## Monitoring

Monitoring will be done by personal visits from a clinical monitor according to SOPs of the IZKS.

To initiate the trial, the monitor will visit the participating local trial site. The monitor shall ensure that the investigators and their staff understand all requirements of the protocol and their regulatory responsibilities.

The monitor will ensure that the investigator will maintain a list of subinvestigators and other appropriately qualified persons to whom he or she has delegated significant trial-related duties (personnel log).

The site will be visited by the monitor at regular intervals to ensure compliance with the trial protocol, GCP and legal aspects. The monitor will review the entries into the CRFs for completeness and correctness and verify the entries on the basis of the source documents. The presence of correct informed consents will be checked for every subject.

Details will be specified in the monitoring manual for this trial.

The investigator must allow the monitor to look at all relevant documents and must provide support at all times to the monitor.

By frequent communications (letters, telephone, fax), the monitor will ensure that the trial is conducted according to the protocol and regulatory requirements.

## Inspection by authorities and ethic committees

Competent authorities and by the sponsor authorised persons (auditor) may request access to all source documents, CRF, and other trial documentation in case of an inspection or audit. Direct access to these documents must be guaranteed by the investigator who must provide support at all times for these activities. Source data documents can be copied during inspection or audit in case the identity of the subject have been made unrecognizable.

## Audits

No audits are planned for this trial.

# Data Management

## Responsibilities

The Data management team is authorised in the case of discrepancies or correction of data errors to contact direct the responsible person at trial site. The queries will be sent by the IZKS Mainz per fax, post or e-mail. For the response the investigator has to comply with a term defined by the IZKS. The investigator has to agree the contact per e-mail or phone.

A detailed methodology for the data management in this trial will be documented in a data management plan that will be dated and maintained by IZKS Mainz*.* This plan has to be signed by the sponsor, the head of the data management team and the responsible data manager. The document may modify the plans outlined in this protocol; however any major modifications of the data handling will also be reflected in a protocol amendment.

## Data collection

This trial will be performed using an electronic case report form (eCRF) or remote data entry (RDE). The investigator and the trial site staff will receive system documentation, training and support for the use of the eCRF. In the case of new trial site staff the training can be performed by personnel of the trial site.

For support with data entry the IZKS Mainz can be contacted.

All protocol-required information collected during the trial must be entered by the investigator, or a designated representative in the eCRF. All data entry, modification or deletion will be recorded automatically in an electronic audit trail indicating the individual subject, the original value, the new value, the reason for change, who made the change and time and date of the change. All data changes will be clearly indicated. Former values can be viewed in the audit trail. All electronic data will be entered by the site (including an electronic audit trail) in compliance with applicable record retention regulations.

The system will be secured to prevent unauthorized access to the data or the system. Only people provided with a user ID and a password will be able to enter or change data. The investigator will maintain a list of individuals who are authorized to enter or correct data and their system ID.

Computer hardware and software (for accessing the data) will be maintained at or made available for the site in compliance with applicable regulations. All technical preconditions for each trial site are record in the DMP.

The system is capable to make exact copies of data in legible paper form for inspections and audits. The investigator, following review of the data in the eCRF, will confirm the validity of each subject’s data by electronic signature or by signing a paper printout of a listing of all subjects enrolled in the trial.

The architecture of the computer system will be described in the data management plan.

## Data handling

During data entry integrity checks help to minimize entry failures. This data entry checks are based on the data validation plan, signed by the coordinating/principal investigator. The data entry system allows the trial monitors to control the entry process with the help of the system-own review functions. Comments and requests can be processed by the trial site just in time.

After completion of data entry the database access will be inhibited and the database will be exported into the data transformation system as mother database.

After completion of data entry the access for data entries is blocked and checks for plausibility, consistency and completeness of the data will be performed. Based on these checks, queries will be produced. Any missing data or inconsistencies will be reported back to the respective site and clarified by the responsible investigator. If no further corrections are to be made in the database it will be declared closed and used for statistical analysis.

All data management activities will be done according to the current Standard Operating Procedures (SOPs) of IZKS Mainz*.*

## Storage and archiving of data

According to GCP, the investigator will archive all trial data (subject identification list, source data) and relevant correspondence in the Investigator Site File (ISF). The ISF, all source data and all documents itemized in section 8 of the ICH Consolidated Guideline on GCP will be archived after finalization of the trial according to the legal regulations.

Responsible for storage and archiving of the trial data (source data and CRFs) will be the principal investigator. After completion of the trial all electronic data will be handed over to the sponsor.

# EthicAL and legal aspects

## Good clinical practice

The procedures set out in this trial protocol, pertaining to the conduct, evaluation, and documentation of this trial, are designed to ensure that all persons involved in the trial abide by good clinical practice (GCP) and the ethical principles described in the Declaration of Helsinki. The trial will be carried out in keeping with local legal and regulatory requirements.

The requirements of the AMG, the GCP regulation, and the Federal Data Protection Law (BDSG) will be kept.

## Patient information and informed consent

Before being admitted to the clinical trial, the subject must consent to participate after being fully informed about the nature, scope, and possible consequences of the clinical trial.

The documents must be in a language understandable to the subject and must specify who informed the subject.

A copy of the signed informed consent document must be given to the subject. The original signed consent document will be retained by the investigator.

The investigator will not undertake any measures specifically required only for the clinical trial until valid consent has been obtained.

If the subject has a primary physician the investigator should inform the subject’s primary physician about the subject’s participation in the trial and if the subject agrees to the primary physician being informed.

After reading the informed consent document, the subject must give consent in writing. The subject's consent must be confirmed by the personally dated signature of the subject and by the personally dated signature of the person conducting the informed consent discussions.

If the subject is unable to read, oral presentation and explanation of the written informed consent form and information to be supplied to subjects must take place in the presence of an impartial witness. Consent must be confirmed orally and by the personally dated signature of the subject or by a local legally recognized alternative (e.g., the subject's thumbprint or mark). The witness and the person conducting the informed consent discussions must also sign and personally date the consent document.

If a subject is not in a position to give informed consent because of his or her physical or mental condition, the consent of a legally authorized representative* must be sought. The consent must be confirmed at the time of consent by the personally dated signature of the representative and by the personally dated signature of the person conducting the informed consent discussions. A copy of the signed consent document must be given to the representative. The original signed consent document will be retained by the investigator. Local legal requirements must be observed and informed consent must be sought from the subject as soon as possible afterwards, if feasible. This procedure must have prior agreement from the independent ethics committee.

Footnote to define “legally authorized representative”

* “Legally authorized representative” means an individual or judicial or other body authorized under applicable law to consent on behalf of a prospective subject to the subject’s participation in the procedure(s) involved in the research.

